# Efficacy of acupuncture on pelvic pain in patients with endometriosis: study protocol for a randomized, single-blind, multi-center, placebo-controlled trial

**DOI:** 10.1186/s13063-018-2684-6

**Published:** 2018-06-07

**Keywords:** Acupuncture, Endometriosis, Pelvic pain, Study protocol

## Abstract

**Background:**

Endometriosis is a chronic gynecological disease that is characterized by the presence of endometrial tissue outside the uterine cavity. The main symptoms include dysmenorrhea, dyspareunia, chronic pelvic pain, and infertility. These symptoms impair the lives of most of the women suffering from the disease. Surgical resection of endometriotic lesions is an effective means of treating dysmenorrhea, but the risk of recurrence is high. Western medicine has limited use for treating it due to side effects and ineffectiveness. The purpose of this study is to verify the effectiveness and safety of acupuncture.

**Methods/design:**

This trial will be carried out in four parts. A total of 106 eligible patients with pelvic pain related to endometriosis will be randomly assigned into two groups, in a 1:1 ratio, as the treatment group or the control group. The participants assigned to the treatment group will be treated with acupuncture treatment at *Guanyuan* (CV4), *Sanyinjiao* (SP6), *Taichong* (LR3), *Zhaohai* (KI6) and *Qichong* (ST30) while the control group will receive acupuncture at non-acupoints. The trial will include three menstrual cycles of treatment and three menstrual cycles of follow-up. The primary outcome is pelvic pain that will be assessed by means of a 10-cm visual analog scale (VAS). At each stage, we will evaluate the safety of the acupuncture treatment.

**Discussion:**

The study will compare the effectiveness and safety of acupuncture with comfort needles on pelvic pain related to endometriosis in the hope of providing significant evidence for using acupuncture on pelvic pain related to endometriosis.

**Trial registration:**

ClinicalTrials.gov, ID: NCT03125304. Registered on 30 April 2017.

**Electronic supplementary material:**

The online version of this article (10.1186/s13063-018-2684-6) contains supplementary material, which is available to authorized users.

## Background

Endometriosis is a chronic gynecological disease characterized by endometrial tissue being present outside the uterine cavity. It occurs in approximately 10% of adolescent girls and women of reproductive age [1]. The main symptom is pelvic pain which includes dysmenorrhea, intermenstrual pain and dyspareunia, which seriously impairs quality of life [2].

The pathogenesis of pain associated with endometriosis is not clear but may be related to inflammation from endometrial lesions, peripheral and central sensitization [3]. Surgical interventions can greatly alleviate pain, but the risk of recurrence is high. The postoperative recurrence rate of endometriosis is 40–50% in 5 years [4]. Drug treatments include oral contraceptives, progesterone, androgen agents and gonadotropin-releasing hormone agonists, but their use is limited because of unacceptable side effects. In a survey involving 1160 women with endometriosis, drug treatment cessation was mostly related to side effects and drug ineffectiveness [5].

Acupuncture, an important component of traditional Chinese medicine, plays a crucial role in disease treatment. Acupuncture is also a popular means of analgesia in traditional Chinese medicine. The analgesic principle of acupuncture is based on the holistic theory of *zang-fu* organs and meridians [6]. Traditional Chinese medicine holds that pain is caused by the stagnation of blood or *Qi* in the uterus. Acupuncture can improve blood and *Qi* circulation, depending on the conduction of meridian acupoints and the function of the central and peripheral nervous system. When the flow of *Qi* and blood is unobstructed, pain can lessen [7]. Some systematic reviews show clinical value in acupuncture for pain [8–10].

One systematic review supports acupuncture for pain relief in endometriosis. However, the evidence for the effectiveness of acupuncture is limited because only a single study was included in this review [11]. Fourteen systematic reviews were included in a Cochrane review, assessing pain relief following intervention with gonadotropin-releasing hormone (GnRH) analogs, ovulation suppression, non-steroidal anti-inflammatory drugs (NSAIDS), surgical interventions, postsurgical medical interventions, alternative medicine (auricular acupuncture compared to Chinese herbal medicine) and anti-TNF-α drugs. The quality of evidence for specific comparisons ranged from very low to moderate. There were limitations in the evidence including a risk of bias in the primary studies, inconsistency between the studies and imprecision in effect estimates [12]. Although acupuncture for pelvic pain in endometriosis has its clinical value, the supporting evidence is limited. Therefore, a randomized, multi-center controlled trial is necessary to provide quality evidence that can guide clinical practice.

### Objective

The purpose of the present study is to demonstrate the efficacy in pain relief and safety of acupuncture in patients with pelvic pain related to endometriosis.

## Methods/design

### Study design

This randomized trial will be conducted in four centers: the Second Affiliated Hospital of Jiangxi University of Traditional Chinese Medicine, the Affiliated Hospital of Jiangxi University of Traditional Chinese Medicine, the Qionghai Hospital of Traditional Chinese Medicine and the Ganzhou Maternal and Child Health Care. A total of 106 patients diagnosed with pelvic pain related to endometriosis will be enrolled in this trial (Additional file 1).

### Participants

Participants will be recruited only if they satisfy all of the inclusion criteria and do not meet any of the exclusion criteria. See Fig. 1 for the participant flow diagram.

**Fig. 1 Fig1:**
[figure not shown]
Participant flow diagram

#### Inclusion criteria

Women aged between 20 and 40 yearsEndometriosis diagnosed according to the Endometriosis Consensus Guidelines (Chinese Medical Association, 2015): (1) symptomatic endometriosis detected by laparoscopy or laparotomy or (2) ovarian endometrioma detected by ultrasound or magnetic resonance imaging with pelvic painPatients willing to receive acupuncture for pain reliefPelvic pain score equal to or above 4 cm on the Visual Analog Scale (VAS)Regular menstrual cycleSigned informed consent

#### Exclusion criteria

Pelvic ultrasound demonstrates that the endometrial cyst measures more than 5 cm in diameter and surgery is indicatedImaging examination suspects pelvic genital malignancyCancer antigen-125 level > 200 IU/LPelvic infectious diseaseOther severe disorders in the heart, lung, liver, kidney, or mental disorders causing inability to cooperate in the studyPatients who have received any other treatment for endometriosis that may affect the observation of the curative effects of acupuncture over 3 monthsPregnancy or breastfeedingRefusal to be randomized

### Interventions

This study has two phases. The first phase will include 3 months of acupuncture treatment, and the second phase will include 3 months of follow-up without treatment. Patients will be randomly assigned to one of two groups in a 1:1 ratio, either the treatment group or the control group. Then, acupuncture treatment will start and last for 3 months following by 3 months of follow-up.

The whole acupuncture treatment will be carried out by two experienced acupuncturists who have received a license from the Ministry of Health of China and have practiced clinically for more than 5 years. Every acupuncture session will be once a day, three times a week and last for 30 min and only start from 7 days before the expected menstrual onset. During the menstrual period, they will receive acupuncture every day when they have endometriosis-associated pelvic pain.

#### Treatment group

The design of the treatment group is guided by the theory of Traditional Chinese Medicine. Disposable, sterile, stainless-steel needles, 0.30 × 40 mm, will be inserted into the acupoints on the abdomen and legs for 15 to 35 mm. The participants assigned to the treatment group will receive acupuncture at bilateral *Sanyinjiao* (SP6), *Zhaohai* (KI6), *Taichong* (LR3), *Qichong* (ST30) and at *Guanyuan* (CV4) for a total of nine needles see (Table 1) [13]. After insertion, all acupuncture needles will be stimulated manually by rotating the needle quickly with the thumb and forefinger to evoke the needle sensation (*De Qi*) once every 10 min.

**Table 1 Tab1:** Acupuncture points

Point	Localization	Muscle	Muscle innervation
*Guanyuan* (CV4)	3 cun caudal to umbilicus	Fibrous tissue, linea alba	Th12
*Sanyinjiao* (SP6)	3 cun proximal to the medial malleolus	Musculus flexor digitorum longus, tibialis posterior	L4–5,S1–2
*Taichong* (LR3)	Depression between the first and second metatarsals	Musculi interossei dorsales	S2–3
*Zhaohai* (KI6)	Depression below the medial malleolus	Abductor of toes	L4–5, S1–2
*Qichong* (ST30)	5 cun caudal to umbilicus, 2 cun proximal to the anterior median line	Obliquus internus abdominis	Th12, L1

#### Control group

The control group will receive acupuncture at non-acupoints. Disposable, sterile, stainless-steel needles will be inserted superficially to a depth of < 5 mm on each shoulder and upper arm, without any stimulation.

### Primary outcome

#### Pelvic pain

The primary outcome is pelvic pain that include dysmenorrhea, intermenstrual pain and dyspareunia. They will be assessed on a VAS scale [14]. On the VAS scale, a 100-mm horizontal line from no pain on the far left to the worst possible pain on the far right is scored by determining the distance from the far left to the edge of the mark made by the patient. The distance represents pain intensity. The VAS will be assessed at baseline, the first, second and third menstrual cycles and the follow-up period. See Table 2 for the study design schedule.

**Table 2 Tab2:** Study design schedule

Period	Inclusion	Treatment			Follow-up		
Visit	1	2	3	4	5	6	7
Menstrual cycle	0 month	1	2	3	4	5	6
Patients	√						
Inclusion and exclusion criteria	√						
Informed consent	√						
Physical examination	√			√			
Medical history	√						
Comorbidities	√	√	√	√	√	√	√
VAS	√	√	√	√	√	√	√
EHP-30	√			√			√
MPI	√			√			√
BDI and POMS	√			√			√
PGIC	√			√			√
Pain diary	√	√	√	√	√	√	√
Patient compliance				√			√
Reasons for dropout or withdrawal				√			√
Adverse events				√			
Safety evaluation							√

*BDI* Beck Depression Inventory, *EHP* Endometriosis-specific quality of life, *MPI* Multidimensional Pain Inventory, *PGIC* Patient Global Impression of Change, *POMS* Profile of Mood States, *VAS* Visual Analog Scale

### Secondary outcomes

#### Endometriosis-specific quality of life

The Endometriosis Health Profile − 30 (EHP-30) [15] will be used to evaluate the effects of endometriosis on patients’ lives. This questionnaire includes two parts. The first part is the core questionnaire applicable to all patients with endometriosis, which includes five dimensions and 30 items. The second part of the modular questionnaire includes 23 items and six dimensions; each dimension is specific to the endometriosis patient: employment, relationship with children, sex, feelings about the medical profession, treatment and infertility. Each item is rated at five grades from 0 as “never” to 4 as “always.” The EHP-30 will be assessed at the baseline period, the third menstrual cycle during treatment and the third menstrual cycle in the follow-up period.

#### Physical functioning

Physical functioning will be assessed by the Multidimensional Pain Inventory (MPI) [16]. This questionnaire includes three parts. The first part is the influence of pain on patients’ daily lives, the second part is the response of patients’ significant other to patients regarding pain, and the third part is the ability of patients to participate in daily activities. Each item is scored at seven grades from 0 to 6. The MPI will be assessed at the baseline period, the third menstrual cycle during treatment and the third menstrual cycle in the follow-up period.

#### Emotional functioning

Emotional functioning will be evaluated by the Beck Depression Inventory (BDI) [17] and Profile of Mood States (POMS) [18]. The BDI consists of 13 items of emotional, behavioral and somatic symptoms. Each item is scored from 0 to 3 and measure sadness, pessimism, sense of failure, lack of satisfaction, guilty feelings, sense of punishment, self accusations, social withdrawal, indecisiveness, body image, work inhibition, fatigability and loss of appetite. The POMS is a psychological rating scale used to assess distinct mood states and measure six different dimensions of mood swings. These include: tension, depression, anger, vigor, fatigue and confusion. A 5-point scale ranging from “not at all” to “extremely” is administered to patients to assess their mood states. The BDI and POMS will be assessed at the baseline period, the third menstrual cycle during treatment and the third menstrual cycle in the follow-up period.

#### Patient satisfaction

The Patient Global Impression of Change (PGIC) [19] will be used to assessed patients’ satisfaction for their changes (improvement or decline) in clinical status. The PGIC is a single-item questionnaire used to assess improvement with therapy. A 7-point scale ranging from “very much better” to “very worse” is used to assess their satisfaction states. The PGIC will be assessed at the baseline period, the third menstrual cycle during treatment and the third menstrual cycle in the follow-up period.

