### Randomization and blinding

One hundred and six eligible patients will be randomly assigned to either the treatment group or the control group in a 1:1 ratio after all baseline assessments. The random allocation sequence was generated by a computer. A researcher who does not participate in treatment, data collection and evaluation will provide the random number and group assignment to each center. The randomization is blinded and allocation is hidden. Owing to the unique nature of the acupuncture operation, it is impossible for the acupuncturists to be blinded. However, patients, the data collector and the statistician will be blinded.

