### Sample size calculations and statistical analysis

This trial will use a clinical-superiority design that aims to verify that the curative effect of acupuncture is better than that of comfort needles. The primary outcome measure is proposed to be the VAS. The minimal important difference (MID) for improvement on the VAS was found to be − 3.9 cm and/or − 49% [20]. According to our pre-experimental treatment of women with pain related to endometriosis, assuming the standard deviation (SD) to be 1.7 and the difference between two treatment effect to be 3, the statistical power is 80% and the significance level is 0.05. According to the formula [21]:$$ N=2\times {\left[\left({Z}_{1-\alpha }+{Z}_{1-\beta}\right)/\left(\delta -{\delta}_0\right)\right]}^2\times {S}^2, $$

where *N* represents size per group, *Z*_1-α_ is Type I error, *Z*_1-β_ is Type II error, *δ* is expected SD of the population being sampled, *δ*_0_ is tolerable error in distance from mean value and *S*^2^ is SD. So it requires each group to contain no less than 44 patients. With an estimated 20% dropout rate, we plan to recruit 53 patients for each group, for a total of 106 patients.

Data will be summarized with counts for categorical variables present as mean and SD for normally distributed variables, or median (interquartile) for the variables not normally distributed. Missing data will be imputed according to the last-observation-carried-forward (LOCF) [22] principle. The data will be subjected to intent-to-treat analysis. A statistician blinded to the group settings will perform the statistical analysis. The between-group difference will be compared by analysis of covariance. The variables not normally distributed will be assessed by the rank-sum test. If participants have taken analgesics during the trial, they will be excluded from the analysis and the rate difference of outcomes between the two groups will be analyzed. Statistical significance will be set at *P* < 0.05.

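### The PGIC rates improvement with therapy but is scheduled before any therapy, and the blanket LOCF rule would carry that rating forward as an outcome for women lost before cycle 3

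*Protocol article*

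**What the plan says.** All references are to the protocol article.

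- **Patient satisfaction, definition:** "The PGIC is a single-item questionnaire used to assess improvement with therapy". The response scale is one of change: "A 7-point scale ranging from “very much better” to “very worse” is used to assess their satisfaction states".
- **Patient satisfaction, timing:** "The PGIC will be assessed at the baseline period", and then at the last treatment cycle and the last follow-up cycle.
- **Table 2:** the PGIC row is ticked at visit 1 (inclusion, month 0), visit 4 (cycle 3) and visit 7 (cycle 6). Text and table agree.
- **Randomization and blinding:** allocation takes place "in a 1:1 ratio after all baseline assessments". The Interventions section starts acupuncture after assignment.
- **Sample size calculations and statistical analysis:** "Missing data will be imputed according to the last-observation-carried-forward (LOCF) [22] principle", and "The data will be subjected to intent-to-treat analysis". Neither sentence exempts an outcome. Groups are compared by analysis of covariance with no covariate named, and by the rank-sum test for variables that are not normally distributed. Expected dropout is 20%, with 53 women per group.

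**The concern.** EHP-30, MPI, BDI and POMS share the PGIC's three time points. They measure a current state, so a baseline value is useful for them. The PGIC asks how things have changed with therapy. At inclusion no trial therapy has been given, so the question has nothing to refer to.

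An unneeded form would be harmless if it were simply filed. The difficulty is that once a baseline PGIC exists in the database, the general LOCF rule can pick it up. The reported cycle-3 and cycle-6 results could then mix real ratings of change with ratings made before treatment began. At stake is the interpretation of one secondary outcome.

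**Working it through.** The protocol states no PGIC figure to reproduce. The check is first one of logic and then an illustration of size.

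**Step 1: Is the baseline rating before all therapy?** Yes. Baseline assessments come before randomization, and randomization comes before acupuncture.

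**Step 2: What can LOCF carry forward?** PGIC ratings are planned at month 0, cycle 3 and cycle 6 only.

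| Time of loss | Last PGIC on file | Value used at cycle 3 | Value used at cycle 6 |
|---|---|---|---|
| Before cycle 3 | Baseline | Baseline | Baseline |
| After cycle 3, before cycle 6 | Cycle 3 | Observed | Cycle 3 |

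Only the first row is a problem. In the second row the carried value is at least a rating made under therapy.

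**Step 3: How many values?** Let d be the share of an arm lost before cycle 3. The protocol gives 20% dropout overall but not its timing, so d is an assumption, varied up to 20%. Affected values per arm = 53 × d:

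- d = 5%: 53 × 0.05 = 2.65, about 3
- d = 10%: 53 × 0.10 = 5.3, about 5
- d = 20%: 53 × 0.20 = 10.6, about 11

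**Step 4: Effect with equal dropout.** Let m be an arm's true mean and b the baseline rating. The mean after imputation is (1 − d) × m + d × b. Assume that b is no change in both arms and that d is equal. The b terms then cancel, and the between-arm difference becomes (1 − d) × (m_T − m_C), that is 95%, 90% or 80% of its true size for d = 5%, 10% or 20%. This treats the women lost as if they would have had the same mean as the others in their arm.

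**Step 5: Effect with unequal dropout.** Assume a 1 to 7 coding with low scores better, no change coded 4, and no true difference (both means 2.5).

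- Losses of 10% (treatment) and 30% (control): 0.9 × 2.5 + 0.1 × 4 = 2.65 against 0.7 × 2.5 + 0.3 × 4 = 2.95. The false difference is 0.30 points in favour of treatment.
- Losses of 15% and 25%: 0.85 × 2.5 + 0.15 × 4 = 2.725 against 0.75 × 2.5 + 0.25 × 4 = 2.875. The false difference is 0.15 points.
- Losses of 30% and 10%: the 0.30 points favour control.

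The error is therefore not always conservative. The coding, the means and the dropout splits are illustrative and do not come from the protocol.

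**The case against.** The strongest reply is that the LOCF rule is a single general sentence in a journal article. It does not say whether a baseline value counts as an observation to be carried forward, and outcome-by-outcome handling is normally set out in a full protocol or SAP, which is not shown. A later document might exclude the baseline PGIC from imputation. That stands as a limit: the consequence follows from the rule as worded, but whether it would be applied that way cannot be confirmed. It does not rescue the schedule, which is stated twice and conflicts with the protocol's own description of the instrument.

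A second reply is that the same section also speaks of changes in clinical status, which a woman could rate for her recent course before treatment. This is a weak defence, because the next sentence ties the item to therapy. It is still a reason not to call the value wholly uninformative.

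A reader might also infer that the baseline PGIC will be an ANCOVA covariate, or that change from baseline in PGIC will be analysed. The protocol states neither. It names no covariate, it offers a rank-sum route with no baseline term that suits a single 7-point item, and it mentions no change score for the PGIC.

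**Conclusion.** The point holds as a minor one. The baseline PGIC does not fit the instrument as the protocol defines it. Under LOCF and intent-to-treat as written, it would stand in for the cycle-3 and cycle-6 results of women lost before cycle 3.

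The likely size is about 3 to 11 values per arm for early loss of 5% to 20%. The matching shrinkage of the difference, to between 95% and 80% of its true size, rests on equal dropout and baseline ratings of no change. A reader might take a 20% dilution as the expected effect. The documents do not support that, because it requires all the planned dropout to fall before cycle 3, and the protocol gives no timing over its three treatment and three follow-up cycles. Unequal early loss could produce a false difference in either direction.

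The PGIC is one of several secondary outcomes. The primary VAS outcome and the sample size are untouched, and the cycle-3 and cycle-6 ratings that are actually observed can still be compared between arms.

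**What to change.** 1. Delete the baseline assessment from the PGIC timing sentence under Patient satisfaction, and remove the visit 1 tick in Table 2.
2. State that the PGIC is compared directly between arms at cycle 3 and cycle 6 with no baseline PGIC term. The rank-sum test already in the analysis section will do; a proportional-odds model is an alternative.
3. State that the PGIC is never imputed from a pre-treatment value.

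The cost is one tick, one edited sentence and one or two added ones. Sites and patients have one form fewer, and no other figure in the protocol changes. The article reports that the trial is recruiting; any baseline PGIC forms already collected can be kept on file and left out of the analysis and the imputation.

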#### Pain diary

Pain diaries will be used to record the specific time and frequency of pain attacks, the duration of pain, the changes of intensity, the start time of pain relief and any medication used for patients. Pain diaries will be assessed at the baseline period, the first, second and third menstrual cycles and at follow-up.

